### Inclusion and exclusion criteria

All eligible pregnant primiparous women between the ages of 18 and 35 years who refer to the hospital for prenatal care at 18-20 weeks of gestation will be requested to participate in the study. Inclusion criteria are having Iranian nationality, having low-risk pregnancy^1^, having no history of infertility and mental diseases, having the ability to read and write, and having smartphone or computer with access to internet and Telegram messaging application.

After the sampling, participants who go into preterm labor, show any signs of high-risk pregnancy, wish to participate in other in-person or virtual childbirth preparation classes than the ones offered at Milad Hospital, and are unwilling to continue with the study will be excluded from the study. However, the educational content will be provided to the excluded samples that are still eager to receive them. In addition, the participants in the study group A who do not send any feedback through Telegram, and the participants in the study group B who do not attend more than two training sessions will be excluded from the study.

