Fourth session: 30-31 gestational weeks	-Risk factors during pregnancy	-Learning the signs of preterm childbirth and how to react to them	1 video clip for theoretical content 9 videos (4) for exercises during pregnancy 1 podcast for relaxation (2)
Fifth session: 32-33 gestational weeks	-Planning for delivery and selecting the type of delivery	-Natural delivery vs. cesarean section -Different pain control methods during labor -Selecting the location and necessary equipment for delivery	2 video clips and 1 PDF file for theoretical content Repeating relaxation (2) Visiting the delivery room in person
Sixth session: 34-35 gestational weeks	-An introduction to vaginal delivery	-An introduction to birth hormones -An introduction to labor stages and self-care at each stage	1 video clip, 1 PDF file, and 2 videos for theoretical content 11 videos for labor and childbirth 1 podcast for breathing techniques 1 podcast for relaxation techniques (3)
Seventh session: 36 gestational weeks	-Postpartum care and breastfeeding	-Postpartum care and recognition of dangerous symptoms -An introduction to breastfeeding methods and breast diseases -An introduction to postpartum exercises	1 video clip, 1 PDF file, and 8 pictures for theoretical content 8 videos for massage during pregnancy and labor Repeating relaxation (3)
Eighth session: 37 gestational weeks	-Neonatal care	-Neonatal care and risk factors	2 PDF files and 2 videos for theoretical content 9 videos for postpartum exercises Repeating relaxation (1)

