The teaching instructors for the training sessions will be midwives who are certified as childbirth educators. If needed, they will use textbooks, video and audio files, music, posters, medical moulages, whiteboard, and slides. Table 1 presents the content, time, and objectives of the educational sessions that are similar for both study groups. To increase the generalizability of the results, another group will be considered as the control group that receives no education about pregnancy and childbirth preparation. It is important to note that all three groups will receive the routine prenatal care provided at the hospital. All participants will also be followed up until delivery.

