### Measurements and feasibility outcomes

The primary outcome of the present study would be the study feasibility that will be assessed based on recruitment and intervention adherence for all of the participants in both groups.

The secondary outcome of the present study would be the improvement of pregnancy experience measured by the brief version of the pregnancy experience scale (PES) [19]. The secondary outcome would be the decreased FOC measured by the version A of Wijma Delivery expectancy/experience questionnaire (WDEQ-A) [20]. In addition, the other outcomes would be the birth preference and type of delivery, respectively. Data collection is shown in the flow diagram (Fig. 1). Data will be collected at 3 times by self-reporting method through Telegram messages: Recruitment (demographic characteristics questionnaire, PES, WDEQ-A) ≈ 18-20 weeks (T1); 36-38 weeks (PES, WDEQ-A, and birth preference) (T2); the first few days of postpartum (type of delivery) (T3).

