### Analytic plan

Feasibility of recruitment will be achieved if ≥ 30% of eligible participants enroll in the study, and ≥ 80% participants complete follow-up assessments at 36-38 weeks (PES, WDEQ-A, and birth preference) (T2); the first few days of postpartum (type of delivery) (T3). Feasibility of intervention adherence will be achieved if average proportion of intervention adherence rate is ≥ 0.8 (participating in six sessions from eight at least for both the virtual and in-person childbirth preparation training groups).

The collected data will be analyzed in the SPSS software (version 19) using descriptive statistics, such as frequency distribution tables. Also, the Chi-square test and one-way analysis of variance (ANOVA) will be used to compare the quantitative and qualitative variables in three groups, respectively. In addition, the paired *t* test will be employed for intragroup comparison. The *p* value of less than 0.05 will be considered statistically significant.

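### Excluding women after enrolment for preterm labor or high-risk signs restricts the type-of-delivery comparison to a selected subset and sits in tension with follow-up of all participants until delivery

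*Protocol article*

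**What the plan says.** All references are to the protocol article.

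- **Inclusion and exclusion criteria.** Those to be excluded once sampling is done include "participants who go into preterm labor, show any signs of high-risk pregnancy". This part is worded once for everyone. The only group-specific exclusions concern adherence. In the virtual group the rule removes "the participants in the study group A who do not send any feedback through Telegram". For the in-person group it reads: "the participants in the study group B who do not attend more than two training sessions will be excluded from the study". Excluded women who still want the educational content will be given it. The section does not say whether their delivery data are still collected.
- **Intervention.** "All participants will also be followed up until delivery". The preceding sentence says that all three groups receive the hospital's routine prenatal care.
- **Measurements and feasibility outcomes.** The primary outcome is feasibility. After pregnancy experience and fear of childbirth, "the other outcomes would be the birth preference and type of delivery, respectively". Data are self-reported through Telegram at three times: T1 (18-20 weeks), T2 (36-38 weeks) and T3 (type of delivery, first days postpartum).
- **Sample size.** The figure of 55 per group comes from type of delivery, with a cesarean rate of 0.55 assumed for primiparous women in Iran and 0.30 under training.
- **Setting.** Controls are women who do not want to give birth at this hospital or attend the classes.
- **Analytic plan.** Feasibility requires that at least 80% of "participants complete follow-up assessments at 36-38 weeks" and at T3.

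**The concern.** Exclusion here depends on something that happens after enrolment and is plausibly tied to the outcome. Preterm labor and high-risk signs can each change how a woman delivers. If these women leave before T3, the plan no longer compares delivery among the women enrolled. It compares delivery among those in whom no complication was detected.

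Three things are at stake. First, the observed cesarean rate would describe a narrower population than the one behind the planning rate of 0.55. Second, the groups are not randomised and have different contact with the study, so the share removed may differ between them and bias the comparison. Third, the completion criterion feeds a primary feasibility verdict, and its denominator is unclear for exactly these women.

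Type of delivery is not the primary outcome, but it is not marginal: it sets the sample size, and the Discussion lists a higher rate of vaginal delivery among the main expected results.

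**Working it through.** **The two statements side by side.** One removes a woman from the study when a complication appears; the other follows every participant to delivery. For a woman with preterm labor or a high-risk sign, the article does not say which governs. The second could mean every participant still in the study, but it does not say so.

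**The plan's own figure.** The only related figure is the type-of-delivery sample size. The printed substitution is (1.96 × √(2 × 0.42 × 0.57) + 0.84 × √(0.55 × 0.45 + 0.3 × 0.7))² / 0.25² = 59.3, not the stated 50. That is a separate matter. What is used below is only the rate of 0.55.

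**Effect of exclusion on the observed rate.** Let p be the true cesarean rate in a group, e the share excluded for these events, and c the cesarean rate among those excluded. Then

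observed rate = (p − e × c) / (1 − e).

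p = 0.55 is from the Sample size section. The article gives neither e nor c. I assume e from 5% to 20% and c from 0.70 to 0.90. These are illustrations, not estimates.

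*Level, any group:*
- e = 10%: (0.55 − 0.07)/0.90 = 0.533 with c = 0.70; (0.55 − 0.09)/0.90 = 0.511 with c = 0.90.
- e = 20%: (0.55 − 0.14)/0.80 = 0.5125; (0.55 − 0.18)/0.80 = 0.4625.
- If c were also 0.55, the rate would stay at 0.55 whatever e is.

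*Spurious difference between two groups with no true effect (p = 0.55 in both):*

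| Excluded, group 1 vs group 2 | c = 0.70 | c = 0.90 |
|---|---|---|
| 10% vs 10% | 0.533 − 0.533 = 0 points | 0.511 − 0.511 = 0 points |
| 5% vs 10% | 0.542 − 0.533 = 0.9 points | 0.532 − 0.511 = 2.0 points |
| 10% vs 20% | 0.533 − 0.5125 = 2.1 points | 0.511 − 0.4625 = 4.9 points |
| 5% vs 20% | 0.542 − 0.5125 = 3.0 points | 0.532 − 0.4625 = 6.9 points |

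Differences are taken before rounding. The group that loses more women looks better, so the sign depends on which group that is.

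*Even exclusion with a true effect.* If e and c are the same in both groups and the planned rates hold, the observed difference is (0.55 − 0.30)/(1 − e), or 0.278 at e = 10% instead of 0.25. Even exclusion creates no difference from nothing, but it does change the quantity estimated.

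**Could exclusion be uneven?** The article gives no event rate for any group, but contact differs. Groups A and B have a fourth session on "Learning the signs of preterm childbirth and how to react to them". Group A's online status is checked and its questions are answered at least twice a day; group B is scheduled for eight sessions. Controls have no training contact between T1 and T2 and do not plan to deliver at this hospital. Against that, every group receives routine prenatal care there.

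**Completion criterion.** Of 165 women, 80% is 132. Suppose 16 women (about 10%) are excluded for these events. If they leave the denominator, 149 remain and 0.8 × 149 = 119.2, so 120 completers are enough. Any count from 120 to 131 would then pass under one reading and fail under the other.

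**The case against.** The strongest reply is that the complication rule is the same for every group and that all three receive routine prenatal care at the hospital, so there is a shared clinical route by which such signs are found. With even exclusion and no true effect the spurious difference is zero. Entry is limited to low-risk women aged 18 to 35, which argues against high event rates. Even the upper figure of about 7 points is well below the planned 25, and it concerns a non-primary outcome of a feasibility study. All of this stands. It limits the size of the problem and makes the between-group bias conditional. It does not remove the selection on post-enrolment events or the unclear follow-up.

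The statement on follow-up can also fairly be read as covering only women who remain in the study. For that reason I call it a tension to be resolved and not a flat contradiction.

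A reader might infer more than the article supports:

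- *That loss is uneven by design.* Only the adherence exclusions are group-specific. Uneven loss from complications is an inference from differences in contact and place of delivery.
- *That the protocol hides harms of the training.* It names no harms and does not link these events to the training. Nor does it say that exclusions will go unreported, and it follows the CONSORT statement for pilot and feasibility trials. A condensed article may also leave harms recording to the full protocol.
- *That all medically indicated cesareans drop out.* An indication first arising in term labor, with no earlier high-risk sign, would stay in the outcome.

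**Conclusion.** The point holds as a design weakness that should be corrected before enrolment. As written, women are removed for post-enrolment events plausibly related to mode of delivery. Type of delivery would therefore be compared in a selected subset, while its planning rate of 0.55 refers to primiparous women generally. What happens to these women's follow-up is not settled by the text.

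Bias between groups is possible, not shown. Under the assumed inputs it is roughly 1 to 7 points if exclusion is uneven. With no true effect it is zero if the same share, with the same cesarean rate, is excluded from each group. The fall in the observed rate occurs in every group whenever the excluded women have a cesarean rate above their group's average. The effect on the 80% criterion depends on a denominator that the article does not define.

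**What to change.** - Reconcile Inclusion and exclusion criteria with the follow-up statement under Intervention by removing preterm labor and high-risk signs as reasons to end study follow-up.
- Separate stopping the training from stopping data collection. Whether a woman continues the training is a clinical matter and nothing is proposed on it here.
- Record type of delivery at T3 for these women and include them in the between-group comparison.
- Report the number of women with each event by group, so that a reader can judge whether the events, or their detection, differed.
- State in the Analytic plan that these women stay in the completion denominator, and show deliveries before T2 as a separate line.

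The cost is small: changes of wording, and continued use of the existing T3 Telegram self-report. The observed cesarean rate will probably be somewhat higher, and some T2 questionnaires will be missing for a stated reason.

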The questions asked on the Telegram room will be answered by the researcher at least twice a day. During the last weeks of pregnancy and after uploading all files, the educational content regarding labor and childbirth preparation methods will be reviewed. To ensure the accurate learning of breathing and relaxation techniques, two 2-h long sessions will be held for the in-person training of the study group A at the hospital along with the fifth and eighth sessions of the study group B. Also, to ensure that the messages are read by the participants, before joining the group, they will be asked to share their last seen status with the researcher. Moreover, they will be required to be online at least once a day to watch the videos or read the messages sent. The last seen time of the participants will be controlled by the researcher, and those who are not online, have not seen the messages, or have not given feedback for 7 days will be contacted by message at first. If no response is received from them, the researcher will contact them through a direct phone call to ask their reasons for not responding the messages. If needed, another cell phone number will be obtained to re-send the Telegram messages to that number. Otherwise, the subject will be excluded from the study.

On the other hand, subjects in the study group B will participate in eight 2-h long sessions during the 20-37 weeks of gestation. The educational sessions will be held at the hospital based on the guidelines of the Ministry of Health. In each session, 1 h will be allocated to teaching theoretical content followed by 45 min of teaching stretching, breathing, and relaxing techniques, as well as practical strategies for posture correction and massage therapy education. The participants will be given 15 min to ask any questions, which will be answered by the researcher.

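### Women who disengage or stop are excluded after enrolment, which on the plain reading biases the adherence and retention criteria upward

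*Protocol article*

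**What the plan says.** The Introduction and Measurements and feasibility outcomes make recruitment and adherence the primary objective and outcome, "assessed based on recruitment and intervention adherence for all of the participants in both groups". The Analytic plan sets the pass marks:

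- **Recruitment:** at least 30% of eligible women enrol, and at least 80% of participants complete T2 (36-38 weeks) and T3 (type of delivery).
- **Adherence:** an average rate of at least 0.8, with adherence defined as at least six of eight sessions in both training groups.

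Other sections remove women after enrolment:

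- **Group A (virtual):** "participants in the study group A who do not send any feedback through Telegram" are excluded. Intervention adds that a woman who is offline, has not seen the messages or has given no feedback for 7 days is messaged and then telephoned. If contact cannot be restored: "Otherwise, the subject will be excluded from the study".
- **Group B (in-person):** "participants in the study group B who do not attend more than two training sessions will be excluded from the study".
- **All groups:** women who "are unwilling to continue with the study will be excluded from the study". The same paragraph removes "participants who go into preterm labor, show any signs of high-risk pregnancy", and women who want other classes.

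Intervention also says: "All participants will also be followed up until delivery". No section says whether excluded women still count in the adherence rate, the completion rate or the group comparisons.

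**The concern.** A feasibility trial asks what share of the women who start will take part and stay. A woman who does not open the Telegram content, stops attending or no longer wishes to take part is a negative answer to that question. If she leaves the study before the rate is calculated, the rate describes those who remain, and the primary outcome is conditioned on itself.

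According to the Discussion, the results are to refine the intervention and support a large-scale grant application. The Introduction names the feasibility of virtual training in Iran as the open question. An adherence figure that omits disengaged women would mislead on both.

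The group comparisons are affected as well. Group A is filtered on Telegram activity, group B on attendance, and control on neither. Differences in PES, WDEQ-A, birth preference or type of delivery could then partly reflect who was kept.

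**Working it through.** **Plan's own figure.** The protocol gives no exclusion rate, so there is no stated result to reproduce. The inputs are 165 women allocated equally to three groups (165/3 = 55 per group), the 0.8 and 80% thresholds, and the 10% drop under Sample size (about 5 of 55). The exclusion counts below are assumptions. I read the adherence rate as the proportion of women attending at least six of eight sessions, and I treat excluded women as non-adherent.

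**Step 1: pass mark with and without excluded women.** With all 55 in the denominator, 0.8 × 55 = 44 adherent women are needed. If e women are excluded and leave the denominator, the minimum is 0.8 × (55 − e), rounded up.

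| Excluded e | Remaining | Minimum adherent | Reported rate | Rate over all 55 |
|---|---|---|---|---|
| 0 | 55 | 44 | 0.80 | 0.80 |
| 5 | 50 | 40 | 40/50 = 0.80 | 40/55 = 0.727 |
| 8 | 47 | 38 | 38/47 = 0.81 | 38/55 = 0.691 |
| 11 | 44 | 36 | 36/44 = 0.82 | 36/55 = 0.655 |

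**Step 2: effect on a fixed true rate.** Reported rate = true rate / (1 − share excluded). For a true rate of 70%:

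- 10% excluded: 0.70/0.90 = 77.8%
- 15% excluded: 0.70/0.85 = 82.4%
- 20% excluded: 0.70/0.80 = 87.5%

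A multinomial simulation (55 women, 200,000 runs) puts the chance of passing the 0.8 rule at about 7% with all enrolled women counted. It rises to 38%, 69% and 93% in these three cases.

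**Step 3: the two readings of the group B rule.**

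- *Attends two or fewer sessions.* Women with three to five sessions stay in and count as non-adherent. Only the lowest attenders disappear, so the inflation is partial.
- *Misses more than two of eight.* The excluded women attended five or fewer, which is exactly the group that fails six of eight. Everyone left is adherent, so the rate is 100% whatever the attendance was. Setting makes this reading possible, because the hospital already requires six of eight sessions.

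**Step 4: retention.** Over 165 women, 0.8 × 165 = 132 must complete. With 17 excluded, 148 remain and 0.8 × 148 = 118.4, so 119 suffice: 119/165 = 72.1%. With 33 excluded, 132 remain and 0.8 × 132 = 105.6, so 106 suffice: 106/165 = 64.2%.

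**Step 5: group comparison with no true effect.** Take the protocol's caesarean rate of 0.55 for everyone enrolled. Suppose a share s of a training group is excluded and their own rate is c (assumed). The retained rate is (0.55 − s × c)/(1 − s).

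- s = 0.10, c = 0.65: (0.55 − 0.065)/0.90 = 0.539, a shift of about −1 point.
- s = 0.20, c = 0.85: (0.55 − 0.17)/0.80 = 0.475, a shift of −7.5 points.

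If excluded women had a rate below 0.55, the shift would go the other way. The protocol gives no basis for choosing between them.

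**The case against.** The best defence is that the Analytic plan gives thresholds without saying that excluded women leave the count. Measurements and feasibility outcomes refers to all participants, Research design and sampling cites the CONSORT extension for pilot and feasibility trials, and analysis sets are often defined in a fuller document. That leaves an all-enrolled count open. But the article does state a rule, exclusion from the study, and its plain meaning is removal. No section offsets it, so this is more than missing detail.

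Other objections have force:

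- The follow-up sentence can be read as covering women still in the study, and the 7-day procedure as the way the no-feedback rule is applied. Neither need be a flat contradiction, but the text does not say so.
- Leaving when unwilling to continue is ordinary withdrawal, in line with Ethical considerations. It should still count as loss in a retention rate.
- Exclusions for preterm labor, high-risk signs, other classes and unwillingness apply to all three groups. Preterm labor and high-risk signs are not adherence failures and bear mainly on type of delivery.
- The size is assumed. At about the planned 10% drop, the pass mark falls to a true 73%, roughly half the fall seen with 11 excluded.

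A reader might infer that the trial cannot fail its feasibility test or that 80% retention is close to automatic. The documents do not support this. With 10 of 55 excluded, 35/45 = 0.78 still fails, the 30% enrolment criterion is settled before any exclusion, and women who stay but miss T2 or T3 still count against completion. Nor are the controls unselected: under Setting they are women who do not want the classes or a birth at this hospital.

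**Conclusion.** The point stands. Followed as written, the protocol removes after enrolment women who count against its adherence and completion criteria, and on the plain reading both rates are biased upward. With 5 to 11 of 55 excluded, the 0.8 rule is met at a true adherence of about 73% to 65%. This rests on three assumptions: the exclusion counts, excluded women being non-adherent, and excluded meaning out of the denominator.

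A reader might infer that group B adherence is 100% by definition. That holds only if the rule means missing more than two of eight sessions and adherence is the share of women reaching six. The literal wording, attending two or fewer, gives partial inflation.

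For the group comparisons, it is certain only that the engagement filters differ between A and B and are absent in control. They add post-enrolment selection of unknown size and direction to a comparison already weakened by non-random allocation and self-selected controls.

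**What to change.** 1. In Inclusion and exclusion criteria and in Intervention, replace exclusion for non-engagement, low attendance or unwillingness with a recorded status: non-adherent, stopped training, or withdrawn.
2. In the Analytic plan, make all enrolled women the denominator: those in each training group for adherence, and those in all groups for T2 and T3 completion. Disengaged women count as non-adherent, and women without T2 or T3 data count as not completed.
3. Collect T2 and T3 from every woman who has not withdrawn consent.
4. Analyse PES, WDEQ-A, birth preference and type of delivery by original group, with adherent women as a labelled secondary set.
5. State which reading of the group B rule is meant and how the two group A passages relate. Reconcile these with the follow-up sentence in Intervention, the reference to all participants in Measurements and feasibility outcomes, and the Analytic plan.

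The cost is protocol wording and a few extra Telegram messages or calls. The reported feasibility figures may be less favourable.
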